**Study Protocol**

**Title:** Comparative effectiveness and tolerability of boceprevir vs. telaprevir and re-assessment of treatment duration in patients with chronic hepatitis C.

**Duration of Study:** Approximately 48 months

**Objectives:**

**Primary Objective:** The primary objective is to study the comparative tolerability of boceprevir vs. telaprevir in HCV treatment in treatment naïve and treatment experienced veterans.

**Secondary Objectives:**

1. To study the comparative effectiveness of boceprevir vs. telaprevir in HCV treatment in treatment naïve and treatment experienced veterans.
2. Other secondary objectives include recording of differences in resource use, such as direct costs (e.g., drug acquisition costs) and other indirect cost (e.g., staff utilization etc.)

**Background:**

An estimated 170 million people worldwide are infected with hepatitis C and 4 million of them are in the United States. Around 85% of patients who become infected with hepatitis C fail to clear the virus and become chronic carriers. Among these individuals, 5%to 20% are reported to develop cirrhosis over a period of approximately 20 to 25. For almost a decade, the standard of care (SOC) in patients with chronic hepatitis C has consisted of a 24–48 week course of PEG-IFN-α2a or PEG-IFN-α2b in combination with ribavirin. This therapy leads to a sustained virologic response (SVR) in 42–52% for HCV genotype 1, 65–85% for HCV genotypes 4, 5 or 6 and 76–82% of individuals infected with HCV genotypes 2 or 3.

During the past 10 years, intensive efforts have been made to develop different compounds with antiviral activities against HCV genotype 1, which are referred to as direct acting antiviral agents (DAAs). The clinical development program of the two HCV nonstructural (NS) 3/4A protease inhibitors boceprevir and telaprevir has now been completed. Few reviews, including narrative reviews and randomized trials have been published so far. Their overall conclusion is that adding one of the protease inhibitors to the standard treatment increases the number of SVRs up to 75% in patients who relapse and 40 – 52 % in patients who didn’t respond.

**Scientific Rationale:**

Both of these drugs have recently been approved by the FDA and are now beginning to be used at the Cleveland VA for the treatment in Hepatitis C, genotype 1. However, the effectiveness and safety of these protease inhibitors within the VA population remain undefined. Since the vast majority of the Hepatitis C patient population at the VA is genotype 1 (approx. 80%), results from this trial will have a significant impact on our treatment recommendations for this population.

The prevalence of HCV infection in VA population is ~60% in persons between 50-60 years old, which means that in 3-5 years, a larger proportion of the VA population with HCV infection will be over 65 years. Furthermore, discontinuation rate in the studies with highly selected population is around 20%; however, we expect this rate to be significantly higher in our population. In addition, older age, multiple co-morbidities and complex drug regimens can have a major impact on treatment effectiveness.

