**Methodology:**

Boceprevir and telaprevir (in combination with peg-interferon alpha 2a and ribavirin [PR]) will be randomly assigned in a 1:1 using a variable block randomization sequence. Boceprevir or telaprevir will be administered through regular clinical care without masking (open label) in previously untreated as well as treatment experienced patients with HCV genotype 1, to be conducted in conformance with Good Clinical Practice (GCP).

This trial consists of two parallel groups: group 1- Boceprevir + PR; group 2 – Telaprevir + PR;

**Type of Blinding:** open-label; however, blinded adjudication of key outcomes, such as adverse events leading to treatment discontinuation, and decisions on treatment cessation due to viral failure will be carried out.

**Allocation concealment:** serially numbered, opaque, sealed envelopes; variable block randomization.

**Sample Size (Including Ratio of Subjects Assigned to Treatments)/Power:** This study is projected to enroll a total of 200 subjects (100:100) in group 1 and 2 respectively.

Given a power of 80% and confidence level of 95% with p-value of 0.05, to determine a 20% difference in tolerability between both drugs, a sample size of 182 is required. Accounting for losses to follow-up, an increase of 10% to the sample size is projected.

**Randomization:** Subjects will be randomized in the two treatment arms in a 1:1 ratio. Randomization will be based on a computer-generated random code.

**Stratification:** Eligible patients will be stratified into 4 groups (treatment naive, treatment experienced; with and without compensated cirrhosis).

**Diagnosis and Criteria for Inclusion:** Adult subjects with CHC HCV genotype 1.

The subject must meet ALL criteria listed below for entry:

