**Inclusion Criteria:**

1. At least 18 years of age
2. Have HCV genotype 1 infection and evidence of chronic hepatitis, as confirmed by a liver biopsy completed within three years prior to enrollment in the study (standard of therapy). Patients with compensated liver cirrhosis will be eligible. Patients who have previously been treated under standard of care (Peg-IFN, Ribavrin) and were non-responders, partial responders, or relapsers will also be eligible.
3. Platelet count ≥ 60,000/mm3; absolute neutrophil count ≥ 1000/mm3 ; hemoglobin ≥11.0 g/dL for females or ≥12.0 g/dL for males; serum creatinine </= 1.5 mg/dL
4. Adequately controlled DM
5. Normal or adequately controlled TSH on prescription medication
6. All other clinical laboratory values within normal limits, unless judged not clinically significant by the investigator
7. Capable of understanding instructions, adhering to study schedules and requirements, and willing to provided informed consent

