**Statistical Methods:**

Descriptive statistics will be used for rates (SVR, RVR, end of treatment response, adherence). The primary and secondary endpoints will be determined on an intention-to-treat (ITT) basis. SVR response rates will be analyzed using chi-square test. Equivalency of response rates for the secondary analysis (reduction in treatment length) will be defined as SVR rates that are within the 10% boundaries compared to standard of care. No interim analyses will be performed. As the study is carried out within the regular hepatitis clinic in an unblinded fashion with FDA approved drugs, no data and safety monitoring board will be necessary. Resource use will be prospectively recorded in disaggregated form. Formal cost-effectiveness analysis will be carried out at the end of the study.

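### SVR is to be compared by a plain chi-square test that cannot use age, co-morbidity or the trial's own strata: a valid test, but one that gives up some precision

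*Protocol*

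**What the plan says.** The Scientific Rationale explains why results from selected trial populations may not carry over to veterans, and says that "older age, multiple co-morbidities and complex drug regimens can have a major impact on treatment effectiveness". Entry is broad on age: the first inclusion criterion is "At least 18 years of age", with no upper limit. Diabetes is admitted if adequately controlled. Age and diabetes status must therefore be known for every patient before entry.

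Under Methodology, "Eligible patients will be stratified into 4 groups (treatment naive, treatment experienced; with and without compensated cirrhosis"). Neither age nor co-morbidity is a stratum.

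Under Statistical Methods, "SVR response rates will be analyzed using chi-square test". The section mentions no adjusted or stratified analysis. SVR is the effectiveness endpoint, and effectiveness is a secondary objective. No between-arm test is named for tolerability, the primary objective.

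**The concern.** The protocol names patient characteristics that may matter for effectiveness, and then fixes for that endpoint a test that takes only arm and response. Leaving the matter to a statistical analysis plan would have raised no issue, but here a specific unadjusted method is stated.

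Two things are at stake. First, baseline values that predict SVR would shorten the confidence interval if they were used, and they are collected anyway. Second, stratified blocks balance prior treatment and cirrhosis but not age or diabetes. If the arms differ in age by chance, the protocol leaves no planned response. In an open-label trial, covariates chosen after the data are seen will be open to challenge.

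**Working it through.** **Inputs.** From Methodology: 100 per arm, and "Subjects will be randomized in the two treatment arms in a 1:1 ratio". The design assumes 80% power at the 0.05 level, and the protocol states that, "to determine a 20% difference in tolerability between both drugs, a sample size of 182 is required". The only discontinuation figure comes from the Scientific Rationale: "discontinuation rate in the studies with highly selected population is around 20"%. Assumed: a two-sided test, the arm rates, and covariate strength. The protocol states no target difference for SVR, so the 20-point tolerability contrast serves only as a yardstick for a binary endpoint at this trial's size.

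**1. The stated sample size.** For 20% v 40%, n per arm = [1.96√(2·0.3·0.7) + 0.8416√(0.16 + 0.24)]² / 0.2² = 3.249/0.04 ≈ 81.2, so 82 per arm and 164 in total. With continuity correction it is 91 per arm, or 182, the stated figure. For 30% v 50% with unpooled variance, (0.21 + 0.25)·7.849/0.04 ≈ 90.3, so 91 per arm and again 182. Adding 10% gives 182 × 1.1 = 200.2. No stated figure is wrong.

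**2. How often chance imbalance occurs.** With 100 per arm, a standardised baseline difference has SD √(2/100) = 0.141. The probability that it exceeds 0.2 SD is 2(1 − Φ(0.2/0.141)) = 15.7%. For at least one of three independent factors it is 1 − (1 − 0.157)³ = 40%.

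**3. What such imbalance does to the estimate.** For a binary factor with prevalence 30% to 50%, the between-arm difference has SD √(2q(1 − q)/100) = 6.5 to 7.1 points, so a 95% range of about ±13 to ±14 points. If the factor shifts the outcome by 10, 20 or 30 points, the unadjusted difference moves by up to about 1.3–1.4, 2.5–2.8 or 3.8–4.2 points. The standard error of that difference is √(0.16/100 + 0.24/100) = 6.3 points at 20% v 40%, and 6.8 points at 30% v 50%.

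**4. Power gained by adjustment.** If covariates explain a share R² of outcome variance, the effective size is 100/(1 − R²) per arm. Power depends on the rates through p(1 − p), so 30% v 50% also stands for SVR of 50% v 70%.

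| R² (assumed) | 20 v 40% | 30 v 50% | 40 v 60% |
|---|---|---|---|
| 0 | 87.6% | 82.8% | 81.2% |
| 0.05 | 89.2% | 84.7% | 83.2% |
| 0.10 | 90.7% | 86.6% | 85.1% |
| 0.20 | 93.7% | 90.2% | 89.0% |

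For scale, a factor with 50% prevalence and a 20-point effect on an outcome averaging 30% has R² = 0.25 × 0.04/0.21 = 0.048.

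**5. Simulation.** 20,000 trials per setting, 100 per arm, two factors of 50% prevalence, unadjusted test against a covariate-adjusted risk difference with robust standard error:

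- No true difference: type I error 5.0–5.1% with either method.
- 20-point true difference: mean estimate 0.200 with either method.
- Power rises from 88.1% to 88.5% if each factor has a 10-point effect, and from 87.9% to 91.0% if each has a 20-point effect.

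A second simulation used SVR-like rates (55% v 75%), 91 per arm, 3,000 trials per setting and one continuous covariate with log-odds slope 0.5, 0.75 or 1.0 per SD. Power was 81–82% unadjusted, and 83%, 86% and 87% adjusted. The ratio of adjusted to unadjusted variance was 0.94, 0.90 and 0.85.

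**6. The cost of a long list.** With six covariates of which only one is informative, the variance fell by about 7% at slope 0.75 and by 1–4% at slope 0.5, but rose by 1–3% at slope 0.25. An uninformative covariate costs roughly 1/N in variance, so four of them with 200 patients would cost about 4/200 = 2%, or 1% in interval width.

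**The case against.** The strongest reply is that nothing in Statistical Methods is incorrect. A chi-square test on an intention-to-treat comparison of randomised arms is valid, and its standard error already allows for chance imbalance. A 0.2 SD imbalance with a log-odds slope of 0.5 shifts the risk difference by about 2.3 points, well inside one standard error. Covariate lists usually belong in a statistical analysis plan. All of this stands, except that the protocol is not silent on the SVR analysis: it names an unadjusted test.

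Four stronger readings that a reader might infer are not supported:

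- **That the SVR result would be biased or the test invalid.** Step 5 shows the same mean estimate and the same type I error either way.
- **That the primary analysis is at fault.** The chi-square is stated for SVR only. No unadjusted test is fixed for tolerability.
- **That the protocol declares age and co-morbidity to be major prognostic drivers.** It says only that they can have a major impact, in a passage about generalising to veterans. It gives no effect size and does not mention haemoglobin or platelet count there.
- **That adjustment always narrows the interval.** Step 6 shows a small loss when a long list carries little signal.

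**Conclusion.** The point holds as a modest loss of efficiency in the SVR comparison. The stated test cannot use age, co-morbidity or the two stratification factors, although the protocol itself gives reason to expect that some of these matter.

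For a 20-point difference with 100 per arm, the loss is roughly 0 to 3 power points if the covariates are weak to moderate, 3 to 4 at R² = 0.10, and 6 to 8 at R² = 0.20. These figures rest on assumed covariate strength, assumed arm rates and a two-sided test. The documents do not show where in this range the trial will fall. The change is worth making because it costs almost nothing, not because the planned analysis is unsound.

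**What to change.** In Statistical Methods, replace the SVR sentence with wording to this effect: SVR will be compared between arms by logistic regression with arm, prior treatment (naive or experienced), compensated cirrhosis, age (continuous) and diabetes status, reported as a standardised (marginal) risk difference with 95% confidence interval; the unadjusted chi-square test is a sensitivity analysis. Fix this list before any outcome is seen.

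Keep the list short. Diabetes is a partial measure of co-morbidity, chosen because it is already known from eligibility. Adding age and co-morbidity as binary strata instead would make 16 cells of about 200/16 = 12.5 patients, which is not advisable. Five coefficients are affordable: even at 75% SVR there would be 50 non-responders among 200 patients, or ten per coefficient.

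The same model is advisable for the primary tolerability outcome, as a recommendation only.

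Cost: one sentence, slightly more analysis work, no extra patients, visits or data, and a negligible loss of precision if the covariates prove uninformative.

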**Methodology:**

Boceprevir and telaprevir (in combination with peg-interferon alpha 2a and ribavirin [PR]) will be randomly assigned in a 1:1 using a variable block randomization sequence. Boceprevir or telaprevir will be administered through regular clinical care without masking (open label) in previously untreated as well as treatment experienced patients with HCV genotype 1, to be conducted in conformance with Good Clinical Practice (GCP).

This trial consists of two parallel groups: group 1- Boceprevir + PR; group 2 – Telaprevir + PR;

**Type of Blinding:** open-label; however, blinded adjudication of key outcomes, such as adverse events leading to treatment discontinuation, and decisions on treatment cessation due to viral failure will be carried out.

**Allocation concealment:** serially numbered, opaque, sealed envelopes; variable block randomization.

**Sample Size (Including Ratio of Subjects Assigned to Treatments)/Power:** This study is projected to enroll a total of 200 subjects (100:100) in group 1 and 2 respectively.

Given a power of 80% and confidence level of 95% with p-value of 0.05, to determine a 20% difference in tolerability between both drugs, a sample size of 182 is required. Accounting for losses to follow-up, an increase of 10% to the sample size is projected.

**Randomization:** Subjects will be randomized in the two treatment arms in a 1:1 ratio. Randomization will be based on a computer-generated random code.

**Stratification:** Eligible patients will be stratified into 4 groups (treatment naive, treatment experienced; with and without compensated cirrhosis).

**Diagnosis and Criteria for Inclusion:** Adult subjects with CHC HCV genotype 1.

The subject must meet ALL criteria listed below for entry:

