**Duration of Treatment:**

Group 1 – Boceprevir (according to product labeling):

- HCV treatment naïve patients: boceprevir for 24 to 44 weeks; PR for 28 to 48 weeks depending on RVR achievement at week 4 of protease inhibitor treatment;
- Relapsers and partial responders: boceprevir for 36 weeks; PR for 36 to 48 weeks depending on RVR achievement at week 4 of protease inhibitor treatment;
- Prior non-responders, or patients with compensated cirrhosis: boceprevir for 44 weeks; PR for 48 weeks

Group 2 – Telaprevir (according to product labeling):

- HCV treatment naïve patients/relapsers: telaprevir for 12 weeks, PR for 24 or 48 weeks depending on RVR achievement at week 4 of protease inhibitor treatment;
- Non-responders and patients with compensated cirrhosis: telaprevir for 12 weeks, PR for 48 weeks

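### Prior-response class is neither a randomisation stratum nor part of the SVR test, although the protocol's own figures show it to be prognostic among experienced patients; this costs some precision but is not bias

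*Protocol*

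**What the plan says.** Under Methodology, Stratification: "Eligible patients will be stratified into 4 groups (treatment naive, treatment experienced; with and without compensated cirrhosis". Beside the variable-block randomisation in the same section, the natural reading is that these four groups are the randomisation strata.

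Inclusion criterion 2 admits previously treated patients who "were non-responders, partial responders, or relapsers will also be eligible", so all three types fall into the experienced level.

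The Background reports that adding a protease inhibitor gives "SVRs up to 75% in patients who relapse" and "40 – 52 % in patients who" did not respond.

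Duration of Treatment sets length by prior response:
- Boceprevir arm: "Relapsers and partial responders: boceprevir for 36 weeks; PR for 36 to 48 weeks", against "Prior non-responders, or patients with compensated cirrhosis: boceprevir for 44 weeks; PR for 48 weeks".
- Telaprevir arm: "HCV treatment naïve patients/relapsers: telaprevir for 12 weeks, PR for 24 or 48 weeks", against "Non-responders and patients with compensated cirrhosis: telaprevir for 12 weeks, PR for 48 weeks".

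The objectives name treatment-experienced veterans for both tolerability (primary) and effectiveness (secondary). Statistical Methods states a chi-square test for SVR and mentions no stratum or covariate.

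**The concern.** By the protocol's own account, a patient's type of prior response bears on the chance of SVR and, without cirrhosis, on planned exposure. It enters neither the allocation nor the stated SVR test. Using the four existing strata in the analysis would not help, because the imbalance arises inside the experienced level.

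If one arm draws more relapsers by chance, its SVR among experienced patients rises for a reason unrelated to the drug. Planned exposure can shift as well, which might affect the opportunity for intolerance. In a trial of 200 the experienced group may be small enough for such draws to be fairly common. What is at stake is the precision of the comparison in experienced patients and how easily its result can be read.

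**Working it through.** **Figure in the plan.** The protocol gives no figure on this point. Its only sample-size figure, 182, does not depend on strata. Taking 20% against 40% (the 20% is the discontinuation rate in Scientific Rationale, used here as the base rate), two-sided alpha 0.05, 80% power and a continuity correction gives 91 per arm, or 182. Nothing below changes it.

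**Inputs from the protocol.** SVR of 75% in relapsers (a ceiling) and 40–52% in patients who did not respond. The gap is 75 − 52 = 23 to 75 − 40 = 35 points.

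**Assumptions, because the protocol gives neither figure.** m experienced patients per arm and relapser share q. The main case is m = 50, q = 0.5. For simplicity all other experienced patients are given the 40–52% rate.

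**Step 1: chance of imbalance.** With the experienced patients split equally between arms, the number of relapsers in one arm is hypergeometric.

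| Experienced per arm | Relapser share | P(imbalance ≥ 12 points) | P(imbalance ≥ 20 points) |
|---|---|---|---|
| 50 | 50% | 0.317 | 0.071 |
| 50 | 30% | 0.275 | 0.049 |
| 30 | 50% | 0.439 | 0.196 |

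**Step 2: shift in the SVR difference.** Shift = imbalance × gap.
- 12 points: 0.12 × 23 = 2.8 to 0.12 × 35 = 4.2 points.
- 20 points: 0.20 × 23 = 4.6 to 0.20 × 35 = 7.0 points.

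These apply to experienced patients only. If half of each arm is experienced, a 12-point imbalance moves the whole-trial difference by half as much, 1.4–2.1 points.

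**Step 3: compare with the standard error.** Main case, unadjusted: SE = √(2p(1 − p)/m), with p the average SVR.
- Non-relapsers at 40%: p = 0.575, SE = √(2 × 0.575 × 0.425/50) = 9.9 points.
- Non-relapsers at 52%: p = 0.635, SE = √(2 × 0.635 × 0.365/50) = 9.6 points.

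A 12-point imbalance thus moves the estimate by less than half a standard error.

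**Step 4: gain from accounting for prior response.** Stratified variance = 2[q × 0.75 × 0.25 + (1 − q) × r(1 − r)]/m, with r the SVR of non-relapsers.
- r = 0.40: 2 × (0.09375 + 0.1200)/50 = 0.00855, against 0.00978 unadjusted. Variance falls by 12.5% and SE from 9.9 to 9.2 points.
- r = 0.52: 2 × (0.09375 + 0.1248)/50 = 0.00874, against 0.00927 unadjusted. Variance falls by 5.7% and SE from 9.6 to 9.3 points.

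With q = 0.3 the reductions are 10.3% and 4.6%. The proportional gain does not depend on m.

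**Step 5: type I error.** In 200,000 simulated trials with equal drugs (75% and 40%, q = 0.5), the unadjusted two-proportion test rejected in 5.4% at m = 50 and in 6.2% at m = 25, the latter partly from small-sample discreteness. Among trials with an imbalance of 20 points or more, it rejected in 12% (m = 50) and 10% (m = 25).

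**The case against.** Two relevant prognostic factors are already strata, nothing in the protocol contradicts the four groups, and any factor left out of the strata is left to chance. Randomisation and the ordinary standard error allow for that. This stands. A reader might infer from the gap of up to 35 points that the comparison in experienced veterans is biased. The documents do not support that: the imbalance favours neither arm in expectation, overall type I error stays near 5%, and the 10–12% arises only by conditioning on an unlucky draw.

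A reader might also infer that the primary tolerability comparison is distorted through exposure. That is possible but unquantified, and the route is narrow. Telaprevir itself lasts 12 weeks for everyone, patients with cirrhosis have one fixed schedule per arm, and a relapser on telaprevir may still receive 48 weeks of PR. The sample size is for tolerability overall, and no powered comparison within experienced patients is stated.

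The inputs are also soft. The 75% is an upper value, the rates are pooled over both drugs, and the Background does not say where partial responders fall.

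Finally, adjustment is commonly left to an SAP, which may exist but is not shown. Its absence alone would be no finding. What the protocol does state, however, is a chi-square test for SVR, and a better test is available from data that the site must already establish.

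**Conclusion.** The point holds as a low-cost improvement in precision and does not show an invalid design. Under the main assumptions, the unadjusted comparison in experienced patients has a variance larger than it need be: accounting for prior response would cut it by about 6–13% (about 5–10% with 30% relapsers). A relapser imbalance of 12 points or more is not rare, but its effect on the estimate is small beside sampling error. The 23–35 point gap is a maximum, and the numbers of experienced patients and relapsers are assumptions. The required 182 is unaffected. The four randomisation strata are defensible; the stated SVR test is what merits changing.

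**What to change.** In Statistical Methods, replace the unadjusted chi-square test for SVR with an analysis stratified by or adjusted for prior-response class (naive, relapser, partial responder, non-responder) and compensated cirrhosis. A Cochran–Mantel–Haenszel test with a stratified risk difference would do, or a regression with both factors. State that tolerability will be compared in the same way. Fix this before outcome data are seen. Both factors are needed at entry for eligibility and the duration schedule, so the cost is a sentence or two of text and no new data. The full cross-classification has eight cells averaging 25 patients (200/8), so state in advance how sparse cells will be merged.

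Splitting the experienced randomisation stratum is optional and makes sense only before enrolment. It would give six strata averaging about 33 patients instead of 50, at the price of two more envelope series and more incomplete blocks, particularly among experienced patients with cirrhosis. If it is done, place partial responders consistently with Duration of Treatment, which groups them with relapsers for boceprevir and does not name them for telaprevir. The protocol authors would have to reconcile those groupings first.
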